**Build trust**			
	Find mutual value	I am worried about the safety of the vaccine for my family. What if it made them sick?^a^ Response: I’m concerned about my family’s health too and also feel responsible if something bad was to happen to them.	Hey, so I’m unvaccinated but I’m still gonna go over to my friend’s house who is really strict about people being vaccinated. Response: Hmn, that’s not something I would do. I would respect other’s decisions.
	Respect autonomy	I can’t believe the government is suggesting that everyone should get vaccinated. This is my health, my decision. Response: The choice is yours and only you can make it. What would help you make your decision?	These COVID regulations are ridiculous, next thing you know I’ll have to wear a hazmat suit to go shopping.^a^ Response: You should respect other people’s health and follow the regulations.
	Don’t lecture or persuade (don’t be an expert)	How can they even be sure the vaccine is safe if they made it so fast? It was rushed, who knows what steps they missed!^a^ Response: I think it might have something to do with reducing all the red tape that helped speed things up but I’m not sure. Let’s look into it together!	I am concerned about the side-effects of the vaccine. I heard that they can get pretty bad. Response: Have you looked at the data? I have, and the side-effects are minor. You should look into what can happen if you don’t get the vaccine.
**Offer support**			
	Ask for perspective	My friend has a party but she says I need to be vaccinated to go, not sure how I feel about it? Response: What makes you unsure?	I don’t believe getting a booster vaccine is really necessary.^a^ Response: It’s interesting how you justify putting other people at risk.
	Affirm feelings or perspective; acknowledge past efforts or successes	I’m unsure about whether to take the vaccine, it seems dangerous.^a^ Response: It is good that you are critical and don’t rush into things when you are unsure. Remember when you had to switch to that new medication and felt better when you looked into it more?	Our neighbours were strict with the social distancing thing and one of them got it anyway. And they are both vaccinated! So I just don’t see the point. Response: That’s not how to think about it. Just because they got it doesn’t mean it’s not worth you making any effort.
**Open up**			
	Ask open questions	For now, I don’t want to get the vaccine. Just because everyone else has decided to get it, doesn’t mean that I have to as well. Response: If you were to consider getting the vaccine, what would change your mind?	How would a mask even help against a virus?^a^ Response: Did you look at the evidence?
	Be resilient if the other is right	First we were told not to bother with masks, and then we were told to wear masks everywhere! These backflips don’t help.^a^ Response: That’s true, the changing recommendations about wearing masks did not help. It goes to show how uncertain things were at the beginning.	I’m waiting, that’s all. It takes time to make sure that the vaccine is safe for everyone. Response: Yeah I’ve heard that point before but let’s focus on why it is important that all healthy people should get vaccinated.
**Don’t be sad if it doesn’t work out**			
	Accept negative outcomes (the conversation may not work out)	It’s clear that you and I are not on the same page about this. I have my reasons, you have yours. Response: That’s OK, thanks for helping me understand your reasons. It seems like it doesn’t work out, so let’s leave it there and maybe we can speak again next week?	Look I just don’t think we are ever going to agree on this.^a^ Response: You don’t appreciate my views! But give me one more try and I bet I can change your mind on this one.

^a^Items included in the prestudy survey.

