#### Gain Trust

The first objective focuses on building trust and rapport with the conversation partner to develop or maintain a supportive relationship or establish a partnership. The first of the 3 open conversation skills, *find mutual value*, aims to find points of agreement or shared value between conversation partners to create a sense of partnership, shared identity, or establish a common fate that one can connect or appeal to [69,79]. Finding points of agreement also signals receptiveness and positive collaborative intentions [59]. The second conversation skill, *respect autonomy*, aims to foster empowerment and self-efficacy in the conversation partner by treating them as responsible agents who have autonomy over their choices. Autonomy is considered a primary psychological need in Self-Determination Theory [66]. Further, emphasizing that one has and is responsible for their own choices reduces psychological reactance [69,75,82] and lowers feelings of defiance [83]. Fostering autonomy is a key recommendation in health risk and vaccine communication guides [53,79]. The third conversation skill, *don’t lecture or persuade (don’t be an expert)*, focuses on using language or strategies that avoid perceptions of authoritarian, coercive, or persuasive intent, which can lead to greater reactance to change communication [66,69,75,79,84]. For instance, using hedging (eg, use of “might” or “somewhat”) to soften factual claims has been found to signal collaborative intentions [59].

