## Methods

### Participants and Recruitment

Participants will be recruited to play the game via video or push notifications promoting *The Good Talk!* game on social media platforms (eg, WHO chatbot channels) and advertised via other WHO informational campaigns. Recruitment will be open to all interested individuals worldwide but will be limited to English language speakers. Participants will self-subscribe to the study by accessing the WHO game information web page via the public link or when shared by members in their social network. On the game information page, participants will be asked if, in addition to playing the game, they would like to participate in the research element (a similar approach was used to recruit participants to research elements in other serious web-based games [93,95]). Participants who are not interested in participating in the study will be sent directly to play *The Good Talk!* game; otherwise, they will be asked to opt-in to the study after giving informed consent. Participation in the research element of the game will be restricted to individuals aged ≥18 years. Participation in the study is voluntary, and no remuneration will be offered to complete the study.

Previous studies evaluating the effect of similar serious games on the development of competences report small-to-medium effect sizes averaging around f=0.18 [95,100,105]. A power calculation with a small effect size (f=0.18), power of 0.90, and α=.05 for an analysis of covariance on posttest open conversation skills suggests a total sample size of n=327. We will aim to collect 450 responses (225 per condition) to account for potential technical issues or possible poor-quality data. Data collection will continue until the prespecified sample size for each condition is reached. Preregistration of this study can be found on the Open Science Framework [107].

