The remaining 4 chapters see the participants encounter characters within their close ties who are motivated by reactance (negative affective reaction when one feels personal freedoms are being threatened), skepticism (doubting knowledge or claims), and inertia (opposing change or action) when discussing COVID-19 measures for the social event. As the conversation develops, the player must select from ≥2 conversational responses that affect the participant’s pathway toward the game objective and the points they earn on a Good Talk Meter. The Good Talk Meter increases with response choices that represent good open conversation skills and decreases for those that represent bad open conversation skills. In each chapter, participants are guided by a *Good Talk Guide* who offers advice and reinforces or educates participants about the strategies based on their selections. A brief description of the objective of each chapter is provided in Table 1, and a screenshot of the game interface is shown in Figure 2.

**Table 1 table1:** Brief overview of the goal and open conversation skills for each chapter.

Chapter	Goal
Introduction	The participant is introduced to the objective of the game and asked to select an avatar and an event they would like to plan. An overview of *The Good Talk!* skills is provided to participants along with the definition of what it means to have an open conversation.
Gain trust	The participant converses with someone who is worried about their kids not being vaccinated and whose kids are skeptical about the government’s use of COVID-19 antigen tests. The participant is encouraged to gain the trust of the conversation partner and, in turn, to encourage their partner to use open conversation skills to gain the trust of their children by expressing their concerns, finding mutual value, and supporting their kid’s autonomy.
Offer support	In this chapter, the conversation partner mistrusts the seriousness of the pandemic, is skeptical about the evidence, and does not see a personal need to get vaccinated. The participant is encouraged to ask for the perspective of their conversation partner rather than argue, with the goal to understand their views and to continue the conversation. By acknowledging their partner’s perspective and concerns, the participant is encouraged to find some common ground so that both feel comfortable attending the event.

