## Results

Recruitment and data collection are estimated to commence in early 2023. The efficacy of the study will be analyzed using an analysis of covariance with posttest open conversation skills as the dependent variable, controlling for pretest scores. Partially completed surveys will be included in statistical analysis whenever possible. As a sensitivity check, analyses will be repeated by excluding participants who complete the study less than 2 SDs below the median completion time as a data quality check.

The primary outcome is open conversation skills. The secondary outcomes are self-efficacy and behavioral intention items. Exploratory analyses will examine the effect of the game on implementation intentions as well as potential covariates or subgroup differences based on sociodemographic information or previous experiences with COVID-19 vaccination conversations.

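### Two of the eight fixed posttest skill items echo the game's own slogan or event storyline, so recognition of game cues could add to the primary score in the game arm only

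*Protocol article*

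**What the plan says.** The Results section states "The primary outcome is open conversation skills", to be tested by "analysis of covariance with posttest open conversation skills as the dependent variable, controlling for pretest scores". Under Outcome Measures (Open Conversation Skills), participants rate eight conversation snippets before play and a different eight afterwards, one per skill on each occasion. The footnote to Table 2 marks the pretest items. The unmarked eight are therefore the posttest for everyone in both arms.

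Two of the unmarked items matter here, both keyed as good responses:

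- *Accept negative outcomes*: the reply includes "It seems like it doesn’t work out".
- *Ask for perspective*: the partner's message begins "My friend has a party but she says I need to be vaccinated to go".

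The Introduction gives the game's four-line mnemonic, whose last line contains the phrase found in the first of these items. Table 1 uses that line as the title of the final chapter. In the section on the game, the player organises a birthday party, dinner, dance party or housewarming and meets characters "when discussing COVID-19 measures for the social event". The control arm plays *Tetris*, which the protocol describes as having no content related to the study. The only check of the items that the article describes is review by behavioural science experts.

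**The concern.** The protocol uses different item sets before and after play in order to limit practice effects. A posttest item that repeats the intervention's wording or setting brings a similar effect back, in one arm only. A game player may rate the slogan reply highly because the phrase is familiar from a game that presented it approvingly, whether or not the underlying skill was learned. A *Tetris* player has no such prompt from play.

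The exposure is caused by randomised assignment and comes after the pretest. The pretest score therefore carries no information about it, and giving both arms the same posttest does not cancel it. The shift would go straight into the estimated treatment effect on the primary outcome, in the direction of the primary hypothesis. A positive result would be harder to read as a gain in conversation skill.

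**Working it through.** **1. The plan's sample size.** Participants and Recruitment gives "A power calculation with a small effect size (f=0.18), power of 0.90, and α=.05 for an analysis of covariance on posttest open conversation skills" and a total of 327. Using the noncentral F distribution with two groups and one covariate (df1 = 1, df2 = N − 3, λ = f²N):

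- N = 327: λ = 0.0324 × 327 = 10.59, power 0.9007. No smaller N reaches 0.90, so the stated figure is reproduced.
- N = 450: λ = 0.0324 × 450 = 14.58, power 0.968.

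For two equal groups d = 2f = 0.36. The sample size is not in dispute, and 0.36 serves as the yardstick below.

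**2. The items against the game.**

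| Posttest item (good-keyed) | Matching game content | Pretest item for the same skill |
|---|---|---|
| Accept negative outcomes: contains the slogan phrase | Fourth mnemonic line; final chapter title | Does not contain the phrase |
| Ask for perspective: a party with a vaccination condition | Player organises a party or similar event and discusses COVID-19 measures for it; the *Offer support* chapter practises this skill so that both sides are comfortable attending | About the need for a booster; no social event |

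The first match is verbal and direct. The second is a match of setting only.

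**3. How much this could matter.** The documents give no item SDs, inter-item correlations or cue effects, so the following are assumptions:

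- the eight items are equally weighted with unit SD after pretest adjustment;
- the mean inter-item correlation r is 0.1 to 0.3;
- each cued item shifts by δ = 0.3 to 0.5 SD in the game arm through recognition alone;
- there is no real gain in skill.

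The sum of eight items has variance 8 + 8 × 7 × r = 8 + 56r. With k cued items, composite d = kδ / √(8 + 56r).

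| k | δ | d at r = 0.1 | d at r = 0.3 | Chance of a significant result at N = 450 |
|---|---|---|---|---|
| 1 | 0.3 | 0.08 | 0.06 | 0.14 to 0.10 |
| 1 | 0.5 | 0.14 | 0.10 | 0.30 to 0.19 |
| 2 | 0.3 | 0.16 | 0.12 | 0.41 to 0.25 |
| 2 | 0.5 | 0.27 | 0.20 | 0.82 to 0.57 |

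For example, with k = 2, δ = 0.5 and r = 0.1: 1.0 / √13.6 = 0.27. The nominal chance of a significant result with no effect is 0.05.

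For two items alone to produce the whole planned d, each would need a shift of 0.36 × √(8 + 56r) / 2, which is 0.66 SD at r = 0.1 and 0.90 SD at r = 0.3.

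**4. Cost of a score without the two items.** Suppose the true effect is equal across items and gives d = 0.36 on eight. The per-item effect is b = 0.36 × √(8 + 56r) / 8, and the six-item d is 6b / √(6 + 30r). This gives 0.332 at r = 0.1 and 0.347 at r = 0.3. Power is 0.94 to 0.96 at N = 450 and 0.85 to 0.88 at N = 327.

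**The case against.** A test aligned with what was taught is legitimate, and the primary hypothesis concerns conversations with vaccine-hesitant people, so COVID-specific items are appropriate. The protocol mentions transferable skills as a potential benefit and does not define the outcome that way. All of this stands. The point is limited to shared surface wording and setting.

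The slogan overlap is one clause of an ordinary phrase, and the reply has independent merit: it thanks the partner, accepts disagreement and leaves the door open. That limits the likely size but does not remove the cue, because the phrase can be deleted without losing that content.

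The party item is weaker. In the game the player hosts the event; in the item the partner is unsure about someone else's party, and the rated reply shares no wording with the game text shown. The script is not in the documents, so recall of specific lines cannot be checked. What remains is a shared setting for the same skill.

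A reader might also infer that a third posttest item is keyed against the teaching, because the bad-keyed *find mutual value* reply says "I would respect other’s decisions" while the game teaches respect for autonomy. The documents do not support this. In full, that reply reproaches the conversation partner on behalf of an absent friend. The Gain Trust section defines respecting autonomy as empowering the partner by "treating them as responsible agents who have autonomy over their choices". Table 2 also keys a similar reproach, about respecting other people's health, as the bad example for that very skill. A player who learned the skill would rate the reply down, in agreement with its key.

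**Conclusion.** The concern holds for two of the eight posttest items: clearly for the slogan item, less strongly for the party item. Any recognition effect would favour the game arm, and pretest adjustment would not remove it. Under the stated assumptions, two cued items correspond to roughly a third to three quarters of the planned effect (0.12/0.36 = 33%; 0.27/0.36 = 75%). If only the slogan item is affected, the range is about half that, d 0.06 to 0.14.

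A reader might infer that cues alone could account for the whole planned effect. That would need both items to move by 0.66 to 0.90 SD through recognition, and nothing in the documents supports shifts of that size. The finding justifies a small correction before launch. It does not show that the primary outcome is invalid.

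**What to change.** The article puts recruitment in early 2023 and ethics approval was still pending, so the items can be changed before data collection:

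1. Remove the slogan phrase from the good reply for *accept negative outcomes*, keeping its thanks, acceptance and offer to talk again.
2. Move the *ask for perspective* item from a party to a setting that the game does not use.
3. Repeat the expert review for these two items.
4. Report the primary score without these two items as a prespecified sensitivity analysis.

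The *find mutual value* item needs no change on this account. The cost is two edits, a short repeat review and one additional analysis. The six-item score has slightly lower power, about 0.94 to 0.96 at 450 participants compared with 0.968 for all eight items, if the true effect is equal across items.

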#### Demographic Questions

Participants will be asked to provide their age (in years) and indicate their gender, current level of English fluency, country of residence, and highest level of education obtained.

### Procedure

Participants will first answer the questions regarding their support for COVID-19 vaccination and their past experience speaking with vaccine-hesitant individuals. Participants will then complete a pretest survey containing the 8 open communication skills items and the self-efficacy and behavioral intention items. The experimental group will then play *The Good Talk!* game, which will take approximately 10 minutes to complete. The control group will play *Tetris* for a similar amount of time.

Following the game, participants will respond to a posttest survey containing the open communication skills, self-efficacy, and behavioral intention questions. Participants will also complete the implementation intention questions and a short demographic survey. At completion of the study, participants will be thanked for their time and invited to share the study with their friends. Participants in the control group will be given the option to play *The Good Talk!*. Figure 3 presents the flowchart of the study design and procedure.

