### Strengths and Limitations

*The Good Talk!* game represents an evidence-based behavioral science application based on the theoretical framework of boosting that aims to boost people’s skills and competences rather than target a specific cause of vaccine hesitancy. As such, this approach has the potential to build transferrable skills that can be applied across a variety of situations. Delivering the intervention via a worldwide, publicly available serious game means that it has the potential to reach a broad and diverse audience while using an ecologically valid medium that mimics real-world web-based communications.

Nevertheless, there are potential limitations to the insights that can be drawn from this study. First, as participants will access the study via a public link that is associated with the promotion of the game, it is not possible to blind participants completely from their assigned experimental condition. Although participants will be blinded to their assigned conditions at the initial pretest survey stage, it is not possible to avoid dropouts or potential self-selection to their assigned condition. To limit this effect, all participants will be told that both games are very important for the research and that everyone will get the opportunity to play *The Good Talk!* game. We will also collect data on the number of dropouts and partially complete and completed surveys per condition to evaluate their impact on study completion. Second, the game may attract a diverse set of participants from various backgrounds worldwide, including different levels of English proficiency, experience with COVID-19 vaccination, and social and political contexts. However, as the intention for the game intervention is to reach a broad and diverse audience and be applicable to individuals from a wide range of cultural, economic, and educational backgrounds, the evaluation will also contribute data on the effectiveness of the intervention in a real-world context.

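### Age, gender, English fluency, country and education are asked only after the game and posttest, so they will be missing for participants who leave once they learn their condition

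*Protocol article*

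**What the plan says.** The Procedure section of the protocol article gives the order of data collection. It opens with vaccination support and prior experience: "Participants will first answer the questions regarding their support for COVID-19 vaccination and their past experience speaking with vaccine-hesitant individuals". The pretest follows, with eight skills items, self-efficacy and behavioral intention. Each participant then plays the assigned game. After that: "Following the game, participants will respond to a posttest survey containing the open communication skills, self-efficacy, and behavioral intention questions". The last block is introduced with "Participants will also complete the implementation intention questions and a short demographic survey".

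The Demographic Questions section lists what that block holds. Besides age, participants are to "indicate their gender, current level of English fluency, country of residence, and highest level of education obtained". None of these items is listed among the questions asked before the game.

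Four other places bear on the point:

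- Participants and Recruitment opens the study worldwide "but will be limited to English language speakers".
- Results plans exploratory analyses of covariates or "subgroup differences based on sociodemographic information". It also keeps partially completed surveys in the analysis where possible.
- Strengths and Limitations says that participants do not know their condition at the pretest, and concedes that dropout and self-selection by condition cannot be avoided afterwards. The planned response is to "collect data on the number of dropouts and partially complete and completed surveys per condition".
- The Results paragraph of the Abstract stops recruitment at 450 completers, 225 per group.

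**The concern.** The protocol expects people to leave when they find out which game they have been given. Demographics are asked only after that moment, so they are missing for the group whose departure the protocol worries about.

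Three things are at stake. First, the dropout assessment can count leavers per condition but cannot say whether they differ in fluency, education, age, gender or country, or whether they differ between arms. Second, variables not recorded for leavers cannot enter an imputation or weighting model for the missing posttests. Fluency and education are natural candidates, because the primary outcome is a rating of short written English exchanges. Third, sociodemographic subgroups can be formed only among those who reach the last page. Someone who finishes the posttest and then closes the browser is in the primary analysis but in no demographic one.

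Fluency raises one further point. It is self-reported, and only one arm has just played a game made of written English conversations, so the answer might shift by arm. The other four items cannot change in about ten minutes.

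**Working it through.** **The plan's own figure.** The point concerns timing and changes no sample-size number, but the stated total reproduces. Inputs from Participants and Recruitment: f = 0.18, α = 0.05, power 0.90, analysis of covariance with two groups and one covariate. The noncentrality is λ = f² × N = 0.0324 × 327 = 10.59 on 1 and 327 − 3 = 324 degrees of freedom, which gives power 0.9007. As a cross-check, d = 2f = 0.36 gives 2 × (1.960 + 1.282)² / 0.36² ≈ 162.2, so 163 per arm and 326 in total. The stated 327 is confirmed. At 450 completers the power is 0.968.

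**What exists for whom.** From the order in Procedure:

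| Participant leaves | Prior experience, pretest skills, self-efficacy, intention | Posttest skills | Five demographic items |
|---|---|---|---|
| During the game | yes | no | no |
| After the posttest skills items, before the demographic page | yes | yes | no |
| Not at all | yes | yes | yes |

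**How many could be affected.** The documents give no dropout rate, so the rates below are assumptions. Recruitment stops at 450 completers, so the number randomised is 450 / (1 − dropout), rounded up, and the number without demographics is that figure minus 450.

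| Assumed dropout | Randomised | Without demographics |
|---|---|---|
| 10% | 450 / 0.90 = 500 | 50 |
| 20% | 450 / 0.80 = 562.5, so 563 | 113 |
| 30% | 450 / 0.70 = 642.9, so 643 | 193 |
| 50% | 450 / 0.50 = 900 | 450 |

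**Which planned analyses are touched.**

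- Primary analysis of covariance (posttest skills on condition and pretest): not touched, since it uses no demographic item.
- Subgroups by previous conversation experience: not touched, since that item is asked before the game.
- Covariates and subgroups by sociodemographic information: restricted to people who reach the last page.
- Dropout counts per condition: still possible. A description of dropouts on the five items is not.
- Imputation or weighting for missing posttests: can use pretest and prior-experience items, but not the five demographics.

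**The case against.** The strongest reply is that little of importance is lost. The primary model needs only the pretest. Both secondary outcomes also have a pregame measurement, and so do vaccination support and prior conversation experience. Arms can be compared at baseline on all of these, and so can dropouts with completers. The sociodemographic analyses are labelled exploratory, and the dropout plan promises counts, which need no demographics. All of this stands and limits the weight of the point.

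A reader might infer several stronger things that the documents do not support:

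- **That the primary test is biased or its type I error inflated because of the page order.** Such figures would need dropout rates and fluency effects that the protocol does not give. A comparison of models with and without fluency, both fitted to completers, would also measure the choice to adjust and not the timing of the question. Completers have a fluency value under the present order, so that adjusted model could be fitted without moving any page.
- **That baseline comparability cannot be shown at all.** It cannot be shown for all randomised participants on the five demographic items. It can be shown on the pretest and prior-experience items for anyone who reaches the game.
- **That all five items are contaminated as covariates.** For age, gender, country and education the problem is selective missingness, not altered values. Only self-rated fluency might be affected, and nothing in the documents shows that it would be.
- **That fluency is an eligibility screen asked too late.** The protocol limits recruitment to English speakers but states no fluency threshold.

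What survives is narrower. Adjusting completers for a late-measured covariate does not describe the leavers, cannot weight or impute for them, and omits those who stop between the posttest and the last page.

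**Conclusion.** The point holds as a weakness of data collection that is cheap to remove. The order stated in Procedure makes five baseline characteristics unavailable for those who leave after learning their condition, a loss the protocol calls unavoidable. The damage falls on the description of dropouts, on any model for missing posttests, and on the sociodemographic covariate and subgroup analyses. The primary analysis of covariance is unaffected as written.

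The size depends on a dropout rate the protocol does not state: about 50 people without demographics at 10%, 113 at 20% and 193 at 30%. No figure for bias or type I error is claimed. The flow diagram (Figure 3) is not available in the text reviewed, but the wording of Procedure is clear on the order.

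**What to change.** Move the demographic page to the start, beside the vaccination-support questions and ahead of randomisation. Prespecify English fluency and education as covariates in the primary analysis of covariance, and as predictors in any imputation or weighting model for missing posttests. Report dropouts by condition on all five items as well as by count.

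The Design section describes randomisation of those who agree to take part and does not place it relative to the pretest. The revised text should state that allocation is drawn after the demographic page. The extra loss from a longer opening survey then falls before randomisation and cannot bias the comparison between arms.

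The cost is one reordered survey page, a slightly longer pretest and some additional early loss. The article describes recruitment as not yet begun, so the change can be made before any data are collected. Demographics lost at dropout could not be recovered later.
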